### Recruitment

Wheezing participants will be recruited at the participating primary care centres and participating hospitals. Potential candidates will be identified by their treating physicians and (specialised) nurses at the primary care practices, outpatient departments, paediatric wards or emergency departments during the recruitment and enrolment phase of the study. Subject information sheets on the study will be handed out to these patients and the parents will be asked to contact the research team for more information about participating in the study.

Healthy participants will be recruited through advertisement and distribution of subject information sheets to all parents of 1- to 4-year old toddlers at day-care centres, via centres for youth health care, via general practitioners practices and during pre-operative screening at the outpatient department of the paediatric anaesthesia department of Maastricht University Medical Centre. Also a variety of (social) media will be used for open advertisement.

All recruiting materials and subject information sheets have prior approval of the institutional Medical Research Ethics Committee (MREC).

### Allocation and blinding

The wheezing preschool children that participate in the RCT will be randomly assigned (1:1), with a secure computer-generated block randomisation procedure (block size of 6), into a usual care group and an intervention group. The randomisation will be organised by the Clinical Trial Centre Maastricht (CTCM) and MEMIC (centre for data and information management at the Faculty of Health, Medicine and Life Sciences of Maastricht University and MUMC +). Randomisation is stratified per measurement centre. The participants, treating physicians and the researchers or research assistants involved in conducting the baseline visit are not blinded to the results of the randomization procedure. The assessment of the primary outcomes and secondary outcomes after one year and at the end of the study will be done by researches who were not involved in the recruitment and randomization procedures. These researchers will be blinded towards the allocation in randomisation group and (final) diagnosis of the participants.

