### Exclusion criteria

Wheezing children: presence of chronic and/or inflammatory disease other than asthma (e.g. inflammatory bowel disease, auto-immune disorders, cardiac disease, congenital lung disease, kidney or liver disease), prematurity < 35 weeks gestational age, postnatal need for oxygen, CPAP, non-invasive or invasive ventilation, or mental disability.Healthy children: a history of asthma or wheeze, other chronic and/or inflammatory disease other than asthma (e.g. inflammatory bowel disease, auto-immune disorders, cardiac disease, congenital lung disease, kidney or liver disease), prematurity < 35 weeks gestational age, postnatal need for oxygen, CPAP, non-invasive or invasive ventilation or mental disability.

Children with a recent course of systemic corticosteroids or antibiotics are not excluded from participation, but the baseline visit will be postponed until at least one month after the treatment.

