### Data collection

During the annual visits, various study procedures will be conducted. Each centre in which the study visits take place (the “measurement centres”) has a dedicated team consisting of one or two research nurses, and one or two p that execute all study-related procedures. All study personnel will be trained in the study requirements and study procedures. Standard Operating Procedures (SOPs) will be provided to all study sites to enhance data quality and reduce variability in measurements as much as possible.

Parents will be instructed that their children should refrain from eating, brushing teeth, using inhalation medication, and moderate to severe exercise as much as possible within 60 min prior to the visit. Drinking of water is allowed prior to the tests. Prior to the annual visits, electronic questionnaires will be sent to the parents. In the RCT study group, a subset of these questionnaires will also be sent at three monthly intervals. The parameters that are measured are listed in Fig. 2.

A web-based study management system Ldot (https://nl.ldot.nl/) will be used to monitor the study logistics and guard the process of the research project. Ldot enhances participant retention by sending both automatically generated reminders for study personnel to contact patients, and automatically generated reminders to study participants to attend planned visits (both by e-mail and SMS messages). Also, periodic communications via newsletters and a website will be provided to parents, recruiting doctors, and treating doctors of participating patients.

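### One fixed block size of 6 per centre, with unblinded baseline staff, lets someone who knows the size and tracks the sequence know about a quarter of assignments in advance

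*Protocol article*

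**What the plan says.** The protocol article, under Allocation and blinding, sets 1:1 allocation "with a secure computer-generated block randomisation procedure (block size of 6), into a usual care group and an intervention group". It mentions no other block size. It adds: "Randomisation is stratified per measurement centre". Randomisation is organised centrally by a trial centre and a data centre.

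The same section states that treating physicians, participants and the "researchers or research assistants involved in conducting the baseline visit are not blinded to the results of the randomization procedure". Under Participant timeline, randomisation takes place at that baseline visit, after consent. Under Data collection, each measurement centre "has a dedicated team consisting of one or two research nurses" and a similarly small number of other staff, who carry out all study procedures. The people who assess outcomes later are separate and blinded.

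**The concern.** A central system protects the list. It does not hide the next assignment from someone who knows the block size and has seen the earlier allocations in the same centre. Once three children in a block have gone to one arm, the rest of that block is determined. Here the sequence runs within a centre and a few people see it in order.

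A team that can foresee an arm could, without intending to, bring forward, delay or discourage particular families. The arms would then differ in the kind of child enrolled. The primary outcome, disease control by TRACK, depends on how symptomatic the child is, so such a tilt would look like a treatment effect. Blinded assessment acts after entry and intention-to-treat keeps whoever was entered, so neither corrects it.

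**Working it through.** The protocol gives no figure for predictability, so there is none to reproduce.

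**Inputs from the protocol article.** Block size 6 and 1:1 allocation within centre (Allocation and blinding); 220 children and 20% control under usual care (Sample size). **Assumptions.** An observer who knows the block size and has tracked the centre's sequence; equal-sized centres, their number being unstated.

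**1. Certain assignments in a block of 6.** There are C(6,3) = 20 equally likely sequences.
- 4th known: the first three are alike, 2/20 = 10%.
- 5th known: the last two are alike, 8/20 = 40%.
- 6th known: always, 100%.

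Expected number = 0.1 + 0.4 + 1.0 = 1.5, and 1.5/6 = 25%. The general formula for a block of 2m agrees: 2m/(m+1) = 6/4 = 1.5.

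**2. Best-guess rate.** Expected correct guesses = m + (4^m/C(2m,m) − 1)/2 = 3 + (64/20 − 1)/2 = 4.1 of 6, or 68.3%, against 50% under simple randomisation.

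**3. Children affected.** Each complete block contributes 1.5; an unfinished last block contributes little.
- 3 centres of 73 or 74: 12 complete blocks each, 3 × 18 = 54.
- 5 centres of 44: 7 complete blocks each, 5 × 10.5 = 52.5.
- 8 centres of 27 or 28: 4 complete blocks each plus a remainder, about 48.
- 10 centres of 22: 3 complete blocks plus four children (0.1 certain), 10 × 4.6 = 46.

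Exact counts and simulation together give about 52 to 55 for 3 to 6 centres, and 46 to 48 for 8 or 10. The count depends on where recruitment stops within a block: 9 equal centres would fill four blocks each and give 54.

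**4. What steering on certain assignments could do.** Suppose there is no true effect and that, when the arm is certain, the enrolled child's chance of control is shifted up for one arm and down for the other. A quarter of each arm is affected, so

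spurious difference = 2 × shift × 0.25.

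- Shift 5 points: 2 × 0.05 × 0.25 = 0.025.
- Shift 10 points: 2 × 0.10 × 0.25 = 0.050.

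Simulation with three centres, which allows for unfinished blocks, gives about 2.4 and 5 points. The standard error is √(2 × 0.2 × 0.8/110) = 0.054. By normal approximation the two-sided 5% test rejects about 7% of the time at 2.4 points and 15% at 5 points. Simulations agree within their error (roughly 6 to 8%, and 14 to 15%).

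**5. Effect of varying the block size.** For an observer who knows the set of sizes but not their order (simulation, about 73 children per centre):

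| Block sizes | Certain in advance | Best guess correct |
|---|---|---|
| 6 only | 25% | 68% |
| 4, 6, 8 | about 2% | 68% |
| 6, 8, 10, 12 | about 1% | 65% |

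Varying the size removes nearly all certainty, but little of the ability to guess.

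**The case against.** A reader might infer that enrolment was steered, or that the false-positive rate is 10% to 26%. The documents support neither.

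- **The larger rates rest on a stronger assumption.** They arise if staff act on every best guess. The differences are then 2 × 0.05 × (2 × 0.683 − 1) = 3.7 points and, at a 10-point shift, 7.3 points. Under that model varying blocks help little: rejection falls from about 10% to 8%, and from about 27% to 21%. These rates should not be presented as the result of this design, or as what the fix removes.
- **Staff knowledge of the block size is not stated.** The article prints it, but that does not show that centres had it during recruitment, and the full protocol may say that it was withheld.
- **The scope for steering is limited.** Candidates are identified by physicians and nurses in many practices and hospitals, and nothing says that they see a centre's running sequence. Consent comes before randomisation. The rule that after systemic steroids or antibiotics "the baseline visit will be postponed until at least one month after the treatment" is a fixed rule, not evidence of discretion. What remains is mainly the order and timing of visits.
- **There is partial mitigation.** A multivariable analysis with age, care background, genetic predisposition and region is planned, although Table 2 lists an unadjusted test for the primary outcome.
- **Much recruitment may be over.** The Methodological issues section describes most patients' selection in the past tense.

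These points limit the size of the concern and the reach of the remedy. They do not change the design as written: one block size, per centre, with unblinded baseline staff.

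**Conclusion.** The concern holds as an avoidable weakness that carries a theoretical risk. With a single block size of 6 per centre, 25% of assignments in complete blocks can be known in advance by an observer who knows the size and follows the sequence. That is roughly 46 to 55 of 220 children over the centre numbers tried.

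If only those assignments were steered, with shifts of 5 or 10 points in the same direction at every centre, the spurious difference would be about 2.4 or 5 points and rejection under no effect about 7% or 14 to 15%. The shift sizes are assumptions; nothing in the documents indicates that steering happens or how strong it would be. The finding supports a change to the procedure and a check. It does not support a claim that the result is biased.

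**What to change.** **Remaining randomisations.** In the existing central system, use block sizes varying at random within each measurement centre, for example 6, 8, 10 and 12. Withhold them from centres until recruitment closes, and replace the stated block size in the protocol with wording to that effect. If recruitment has closed, this part no longer applies.

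**Children already randomised in blocks of 6.** Reconstruct from each centre's sequence the probability that each child would be allocated to the intervention, given the earlier allocations. Relate it to baseline API, which the protocol collects at baseline, and to baseline TRACK if it was collected. The text gives TRACK at three-month intervals and the questionnaire schedule is in a figure not shown, so its baseline collection needs confirming. Report the primary result adjusted for that probability as a sensitivity analysis.

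**Cost.** A new list, a short amendment and one extra analysis, with no added children or visits. The possible imbalance within a centre at any moment rises from at most 3 children to at most 6, which matters little for power with about 110 per arm. Guessing is only slightly reduced, so the sensitivity analysis is worth having either way.

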### Participant timeline

Both wheezing participants and healthy participants follow the same timeline (Fig. 1). Participants enrol in the study, after informed consent, at the age of 2 or 3 years old. At the baseline visit, the wheezing children that participate in the RCT will be randomised into either the intervention group or the usual care group. All children included in the study will perform the study-related procedures, including the breath test, at the baseline visit (see section “data collection” and Fig. 2). The children that will be allocated to the intervention arm of the RCT will receive their probability diagnosis and corresponding treatment advice within three months of the baseline visit. All children will be invited for the annual, study-related hospital visits until the age of 6. The performed study procedures at each visit are illustrated in Fig. 2. All parents will receive online questionnaires prior to the annual visit (a list of the questionnaires is provided in Fig. 3). Parents of children that participate in the RCT will also receive questionnaires on disease control and healthcare related expenditures with a 3-month interval. At the age of 6, a final diagnosis will be made based on respiratory symptoms, use of medication, and objective lung function measurements as reported previously [22].

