### Sample size

*Randomised controlled trial* With a presumed percentage of well-controlled preschool children with asthma-like symptoms of 20% in the usual care group (based on reference [32, 33]), and of 40% in the intervention group, 91 patients in both groups are needed to detect this difference with an alpha of 0.05 and a power of 80%. Taking a dropout rate of 10% into account, we aim to include a total number of 220 preschool children with asthma-like symptoms.

*Prospective cohort study* For studies assessing the relationship between microbiome, transcriptomics, epigenetics, and atopic outcomes like asthma, a sample size of 70–80 is considered adequate [34, 35].

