### Questionnaires

Parents will be asked to complete several questionnaires during the study to assess asthma control, quality of life, and utilisation of health care and societal resources [40–42]. The questionnaires will be provided as e-version and will be sent to the parents two weeks before the annual clinical visits. Two questionnaires will be sent at a three-monthly interval: the questionnaires on asthma control (TRACK) and on utilisation of health care and societal resources.

*TRACK* Parents will be asked to complete the TRACK questionnaire at a 3-month interval. The TRACK questionnaire is a validated questionnaire on asthma control specifically developed for use in this age group, independent of the diagnosis. A score of 80 or more is defined as well controlled disease. The TRACK score is sensitive and reliable, and an increase of 10 points was found to be the ‘minimally important difference’ [43].

*ISAAC questionnaire (Core Questionnaire and Environmental Questionnaire)* The Core Questionnaire and the Environmental Questionnaire have been developed by the ISAAC steering Committee [44]. This questionnaire is used in this study to assess asthma, allergic rhinoconjunctivitis and eczema in all participants and to assess a variety of environmental factors.

*EQ-5D-Y (proxy version)* The EQ-5D-Y questionnaire is a validated child-friendly version of the EQ-5D on quality of life that comprises the following five dimensions with three answer levels (“no problems,” “some problems,” and “a lot of problems”): mobility, looking after myself, doing usual activities, having pain or discomfort and feeling worried, sad or unhappy. It also includes a visual analogue scale (VAS), which gives an overall assessment of the child’s health status in a scale from 0 (worst imaginable health state) to 100 (best imaginable health state). In the proxy version, the caregiver is asked to rate the child’s health-related quality of life (HRQoL). The EQ-5D-Y proxy-version has been tested in children as from 4 years of age [45], which revealed that some domains (e.g. self-care) were sometimes perceived by the parents as not suitable to young children. However, no alternative preference-based measure is currently available or has a validated proxy-version for use in preschool children.

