### Assessment of differences in asthma control between the intervention group and the usual care group in the percentage of well controlled asthma-like symptoms after 1- and 2-year follow-up.

The effect of the intervention on asthma control will be assessed by comparing the outcome measures between the intervention and the usual care group in the RCT. Asthma control will be scored using the validated TRACK questionnaire. Differences of the continuous outcome measure between the intervention group and the usual care group will be tested for significance with the unpaired t-test for normally distributed parameters and the Mann Whitney-U test in case of a not-normal distribution.

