A cost-effectiveness analysis will be performed from a societal and healthcare perspective with a time horizon of 2 years. Incremental cost-effectiveness ratios will be calculated as societal cost per QALY (societal perspective) and health care cost per additional child with control of asthma-like symptoms (healthcare perspective). Standard sensitivity- and bootstrap analysis will be performed to address uncertainty regarding costs and cost-effectiveness outcomes. Cost-effectiveness acceptability curves will be constructed reflecting the probability that the diagnostic breath test is cost-effective for a range of threshold values. Costs and effects after one year will be discounted at 4.0% and 1.5% respectively, according to the Dutch guidelines for health economic evaluation [45, 48].

All outcome parameters and corresponding outcome measures and methods of analysis are listed in Table 2. The large number of patients (*n* = 220) allows better representation of specific subgroups of specific age, background (primary or secondary/tertiary care), genetic predisposition, and geographic area. All these parameters will be measured and included in the multivariable analysis in order to assess possible influences on outcome. Intention-to-treat analyses will be applied. We will execute two subgroup analyses: one for age and one for level of care (first-line versus secondary/tertiary care). Two-sided *p*-values < 0.05 (with correction for multiple testing) will be regarded as statistical significant.

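### The primary comparison is fixed as an unadjusted two-sample test although randomisation is stratified by centre and a baseline TRACK score appears to be available: valid, but it gives up precision at no benefit

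*Protocol article*

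**What the plan says.** - **Allocation and blinding:** allocation is 1:1 in blocks of six, and "Randomisation is stratified per measurement centre". The number of measurement centres is not given.
- **Statistical methods, asthma control:** "Differences of the continuous outcome measure between the intervention group and the usual care group will be tested for significance with the unpaired t-test", with the Mann-Whitney U test if the distribution is not normal. Table 2 names the same two tests for the primary outcome, in analysis group I.
- **Questionnaires, TRACK:** "Parents will be asked to complete the TRACK questionnaire at a 3-month interval". A score of 80 or more counts as well controlled. The readable text does not say outright that TRACK is completed at baseline. The three-monthly schedule implies it, and the questionnaire schedule (Fig. 3) is not shown.
- **Statistical methods, health gain and costs:** after listing age, background (level of care), genetic predisposition and geographic area, the article says "All these parameters will be measured and included in the multivariable analysis in order to assess possible influences on outcome". It also commits to intention-to-treat analysis and to two subgroup analyses, by age and by level of care.

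**The concern.** A trial that stratifies its randomisation by centre normally carries centre into the analysis, so that the standard error reflects the design. A trial that measures its outcome scale at entry normally adjusts for that score, because it is usually the strongest available predictor of the same scale later. Here the named primary tests can do neither.

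The multivariable analysis does not fill the gap. Its stated purpose is to look at influences on outcome. Geographic area overlaps with centre but is not the stratification factor, and baseline TRACK is not in the list. The reader also cannot tell whether that model or the two-sample test decides the trial. At stake is power that would need no further children or visits, in a trial of 220 whose recruitment, by the article's own account, was hit by the pandemic.

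**Working it through.** **Inputs from the article (Sample size).** Well-controlled rate: "20% in the usual care group"; "and of 40% in the intervention group". Error rates: "an alpha of 0.05 and a power of 80"%. The test is two-sided. Stated requirement: 91 per group.

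**Step 1: reproduce the 91.** Two proportions, pooled variance:

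n = [1.96·√(2·0.3·0.7) + 0.8416·√(0.2·0.8 + 0.4·0.6)]² / 0.2² = (1.2702 + 0.5323)² / 0.04 = 81.2, so 82.

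Continuity correction: (81.2/4)·[1 + √(1 + 4/(81.2·0.2))]² = 90.95, so 91. This matches the article. At 91 per arm the unadjusted test has 84.3% power without the correction and 80.0% with it.

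**Step 2: what a covariate buys in general.** Adjusting for a covariate with correlation r multiplies the residual variance by (1 − r²), so 91 per arm acts like 91/(1 − r²). A test with 80% power moves to Φ(2.8016/√(1 − r²) − 1.96).

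| r (assumed) | 91 per arm acts like | 80% power becomes |
|---|---|---|
| 0.3 | 100 | 83.6% |
| 0.5 | 121 | 89.9% |
| 0.7 | 178 | 97.5% |

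**Step 3: the binary endpoint, by simulation.** Settings: 91 per arm, 20% v 40%, 10,000 trials per row, least-squares models on the 0/1 outcome. Assumed because the article gives no values: five centres, intracentre correlation 0.05, 30% of children with an asthma label, and a label effect of 0.3 SD (first row) or 0.5 SD (other rows). Here r is the correlation of baseline TRACK with the latent follow-up score.

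| r | Unadjusted | Centre only | Label only | Baseline TRACK only | All three |
|---|---|---|---|---|---|
| 0.3 | 84.6% | 85.0% | 84.6% | 86.3% | 87.0% |
| 0.5 | 84.9% | 85.4% | 85.8% | 89.4% | 91.1% |
| 0.7 | 85.2% | 85.8% | 86.1% | 94.0% | 95.5% |

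A model with arm, centre and baseline TRACK should fall between the last two columns. Smaller runs (1,000 to 1,500 trials per setting) gave adjusted power of 85-88% at r = 0.3 and 89-90% at r = 0.5. Some of their unadjusted values were as low as 82.4%, within Monte Carlo error of 84.3% (standard error about 1.2 points at 1,000 trials). With the margins held at 20% and 40%, unadjusted power does not depend on r.

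With no true effect, rejection was 4.4-5.1% for the unadjusted test and 4.7-5.4% with centre. When the covariates predicted nothing, adjusting for all of them cost under one point (84.5% to 83.8%; 4,000 trials).

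**Step 4: the continuous score, as the named t-test uses it.** If 20% v 40% above 80 is a normal shift, it equals 0.8416 − 0.2533 = 0.588 SD. The unadjusted t-test then has 97.8% power at 91 per arm, rising to 98.6% (r = 0.3) or 99.6% (r = 0.5). For a smaller effect, the article's 10-point minimally important difference, with assumed SDs:

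| SD | Unadjusted | r = 0.3 | r = 0.5 | r = 0.7 |
|---|---|---|---|---|
| 20 | 92.1% | 94.2% | 97.3% | 99.7% |
| 25 | 77.0% | 80.7% | 87.6% | 96.5% |
| 30 | 61.4% | 65.4% | 73.8% | 88.3% |

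**The case against.** **Covariates belong in the analysis plan, and a multivariable model is already promised.** This would stand if the article had left the method open. It names the tests for the primary outcome twice, and neither admits covariates. An analysis plan that adjusted would depart from the published method.

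**Nothing is biased, and the gain may be small.** This stands. The unadjusted test holds its size and is, if anything, slightly conservative against the stratified design. Centre contributes about half a point of power; its main justification is that the analysis should follow the randomisation. The benefit rests on baseline TRACK, whose collection is implied and whose correlation is assumed.

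**A reader might infer that pooling children with the two breath-test labels dilutes the effect, and that an analysis by label is missing.** The article does say "All children included in the study will perform the study-related procedures, including the breath test, at the baseline visit", and the label decides which advice an intervention family receives. But the documents do not support the stronger reading. The trial asks what applying the test does in wheezing preschool children, and both results are part of that intervention, so the pooled comparison is the right primary. Table 2 runs most secondary outcomes in groups I to IV, which are defined only in Fig. 5 (not shown), so a label analysis cannot be called absent. Any figure for dilution needs an effect confined to test-positive children, which the article nowhere assumes.

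Nor would a label analysis be well powered. By the article's 30% prevalence, 84% sensitivity and 82% specificity, 0.3·0.84 + 0.7·0.18 = 37.8% test positive, about 37 of the 99 evaluable children per arm (110·0.9). At 20% v 40% that group has 47% power.

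**Conclusion.** The point holds as a matter of efficiency. The article fixes a covariate-free primary test, stratifies by a factor that this test ignores, and offers no stated treatment-effect model with centre or baseline TRACK.

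For the binary endpoint at 91 per arm, adjustment takes power from about 83-85% to about 85-88% (r = 0.3), 89-91% (r = 0.5) or up to 96% (r = 0.7). For the continuous score at the full design effect it adds only 1-2 points, and more if the true effect is smaller. These figures rest on assumed correlations, SDs, centre numbers and centre effects, and on a baseline TRACK being collected.

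A reader might also take the ignored strata to mean an inflated error rate. The simulations show none.

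**What to change.** Make the primary treatment-effect analysis a regression on arm, measurement centre and baseline TRACK, under intention to treat with both label groups pooled:

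- If the endpoint is TRACK of 80 or more, use logistic regression and report the marginal risk difference with its 95% CI. The result then stays on the percentage scale used for the sample size.
- If the endpoint is the score, use ANCOVA.

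The Outcomes section names a percentage and the test section a continuous score, so the scale must be settled first. State that this model decides the primary outcome and that the existing multivariable analysis is exploratory. Confirm that baseline TRACK is completed before families know their allocation, and say in advance how small centres are combined.

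An effect by baseline breath-test label may be added as a secondary analysis if groups II to IV do not already provide it, with no claim of adequate power.

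The cost is wording and model code, with no extra visits or children. It should be written down before any comparison by arm is seen.
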